### Data analysis plan

Data will be analyzed using the Statistical Package for Social Studies (SPSS 22; IBM Corp., New York, NY, USA). Continuous variables will be expressed as mean ± standard deviation or median and interquartile ranges according to the normality assessment. Categorical variables will be expressed as frequencies and percentages.

The chi-square statistical test will be applied for categorical variables to assess the association between them. The t-test or Mann-Whitney test will be used to compare numeric variables. Repeated measures analysis of variances or Friedman’s test will be used to evaluate repeated measures over the follow-up period.

The incidence rate and cumulative incidence rate will be computed for incidence of T2DM among the intervention and control groups. Additionally, comparison between the incidence of T2DM among different age groups and gender will be evaluated. Kaplan-Meier survival curves and log-rank tests will be used to compare the intervention and control groups as well as the different risk groups for progression to T2DM, and transition and/or relapses from different stages of TTM.

Hazards ratios with 95% confidence intervals will be calculated and the adjustment of known confounders will be adopted in the Cox regression model. In all the analyses, *P*-values < 0.05 will be considered statistically significant.

The principal analyses of primary and secondary outcomes will use the intent-to-treat approach. The intent-to-treat analyses will include all participants in their randomly assigned treatment groups regardless of a participant’s adherence to the assigned treatment regimen.

All data entry will be anonymous and identification numbers will be saved in a password-protected log file with the primary investigator. Backup of entered data will be created monthly to avoid any loss of collected data. An interim analysis of data will be conducted 12 months after recruitment of the last participants. Interim analysis aims to evaluate the completeness and accuracy of the collected data and early detection of any difficulties.

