### Sample size calculation

A sample size of 300 is required so that there are 150 participants each in the intervention and control groups. The sample size was calculated by using Stata® software version 15 (StataCorp, College Station, Texas, USA) with the assumptions that α = level of significance (0.05), β = Type II error (power of the study = 1- β = 80%). The hazard rate of diabetes development among the control group is 10% over the 2 years, the hazard rate of diabetes development among the intervention group is 7% over the 2 years (reduction of about 30%) and the minimum sample size required to reject the null hypothesis is 256 (128 in each group). With an expected loss of follow-up around 20%, the sample size was increased to 300 participants in total.

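### For the repeatedly measured continuous outcomes, Friedman's test has no arm term and repeated-measures ANOVA drops anyone with a missed visit, which conflicts with the intention-to-treat statement

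*Protocol article*

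**What the plan says.** The Data analysis plan gives one sentence on longitudinal outcomes: "Repeated measures analysis of variances or Friedman’s test will be used to evaluate repeated measures over the follow-up period". For two-group comparisons of numeric data it says: "The t-test or Mann-Whitney test will be used to compare numeric variables". That sentence names neither a visit nor the use of the baseline value. For progression to type 2 diabetes the plan is explicit about arms: "Kaplan-Meier survival curves and log-rank tests will be used to compare the intervention and control groups", with hazard ratios from Cox regression.

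The same section commits to intention-to-treat: "The principal analyses of primary and secondary outcomes will use the intent-to-treat approach". It adds: "The intent-to-treat analyses will include all participants in their randomly assigned treatment groups regardless of a participant’s adherence to the assigned treatment regimen".

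The Sample size calculation sets the total at 300 and allows for attrition: "With an expected loss of follow-up around 20" percent. The Methods part of the Abstract schedules a baseline assessment and six later ones, at 6 to 36 months. The last paragraph of the Background describes a parallel-group, 1:1 superiority trial. Under Lifestyle education, both arms receive the same group session, written advice and metformin; only the messages differ.

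**The concern.** The trial asks whether the messages make a difference between arms. For the continuous measures followed over time, the plan names two longitudinal methods, each with a different weakness.

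- **Friedman's test**, the fallback when normality fails, answers whether values changed across visits. It does not answer whether they changed differently in the two arms. Since both arms receive active shared care at baseline, a change over time is likely whether or not the messages work.
- **Repeated-measures ANOVA** can answer the arm question, but in its classical form it needs a value at every visit in the model. It becomes an analysis of completers in a section that promises to include all participants as randomised.

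At stake is the evidence on biomarkers and obesity measures, which the Secondary objectives list, and the long-term effect on biological markers, which the section Time of messaging gives as the purpose of the later visits. If people who leave differ from those who stay, and differently by arm, the completers' comparison loses the protection of randomisation as well as precision.

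**Working it through.** The plan gives no figure of its own for these outcomes. The sample size was set for diabetes incidence and is used here only for its total and its loss allowance.

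**Inputs from the protocol article:** total N = 300; loss about 20% (both Sample size calculation); 7 assessments, of which 6 are follow-ups (Abstract, Methods).

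**Assumed inputs:** rate of sporadically missed visits m = 2%, 5% or 10% per follow-up, independent across visits; baseline-to-follow-up correlation ρ = 0.4 to 0.8; the simulation settings below.

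**Step 1: what Friedman's test uses.** With n participants ranked across k visits and R_j the rank sum at visit j, the statistic is 12/[n·k·(k+1)] × ΣR_j² − 3n(k+1). Arm does not appear in it. A simulation with 150 per arm, 7 visits, between-participant SD 0.3, within-participant SD 0.2, linear changes over follow-up and 1,000 runs per scenario compared it with a test of the arm difference in each participant's linear trend:

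| Scenario | Friedman rejects | Arm-by-time contrast rejects |
|---|---|---|
| Same change in both arms (−0.1 each) | 100% | 4.5% |
| Opposite changes (+0.1 and −0.1) | 3.7% | 100% |

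In a further single data set, shuffling the participants between arms left Friedman's p-value exactly the same (0.262). Running the test separately in each arm does not help: it gives two p-values and no test of the difference between arms.

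**Step 2: what classical repeated-measures ANOVA keeps.** For a model over all visits, the fraction kept is (1 − 0.20) × (1 − m)^6.

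| m per follow-up visit | Fraction kept | Of 300 | Excluded |
|---|---|---|---|
| 0 (stated loss only) | 0.800 | 240 | 60 |
| 2% (assumed) | 0.709 | 213 | 87 |
| 5% (assumed) | 0.588 | 176 | 124 |
| 10% (assumed) | 0.425 | 128 | 172 |

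Only the first row rests on the protocol's own figures. The fraction does not depend on N.

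**Step 3: the single-visit test.** With equal variances, baseline adjustment multiplies the variance of a follow-up-only comparison by 1 − ρ². For ρ = 0.4, 0.6 and 0.8 this is 0.84, 0.64 and 0.36, a reduction of 16%, 36% and 64%. Against a change score, whose relative variance is 2(1 − ρ), the factor is (1 + ρ)/2 = 0.70, 0.80 and 0.90, a reduction of 30%, 20% and 10%. This is a gain in efficiency and does not correct an invalid test.

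**The case against.** The strongest reply is that the sentence on repeated measures never says that it compares arms. It can be read as describing change over time, with the two-group work left to chi-square, t-test or Mann-Whitney, log-rank and Cox. On that reading Friedman's test is a legitimate description. This is fair as far as it goes: the arm-comparison intent comes from the superiority design and the intention-to-treat statement. But if that reading is right, the article names no longitudinal arm comparison for these measures, and the replacement is still needed.

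A second reply concerns intention-to-treat. The qualifier in that statement is adherence, not missing outcomes, and a condensed article may leave imputation to a fuller document. That also stands in part: the conflict arises from the named method as written, without imputation, and silence on missing data is not itself the fault.

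Third, several secondary outcomes are worded as thresholds or stages and would go largely to categorical or time-to-event methods. That limits the reach to the measures analysed as continuous.

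A reader might go further and infer that repeated-measures ANOVA cannot compare arms at all. That is not so, since arm can enter as a between-subject factor. Nor do the documents support calling the t-test or Mann-Whitney test wrong. Both compare randomised arms validly at one visit, and the outcome wording leaves room for change scores.

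**Conclusion.** The point holds for the repeatedly measured continuous outcomes: HbA1c, lipids, blood pressure and weight. Friedman's test cannot test the intervention, whatever the data. Classical repeated-measures ANOVA over all visits keeps at most about 240 of 300 at the stated loss, which does not fit with including all participants. That ceiling assumes that the 20% allowance is realised, that one model spans every visit and that nothing is imputed; a model over fewer visits could keep more. The figures of 213, 176 and 128 rest on assumed miss rates and should not be quoted as forecasts.

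The diabetes-incidence comparison is outside this point, because log-rank and Cox compare arms and use censored follow-up. It would also go too far to say that shared improvement will be reported as an effect of the messages. That would require the named two-group tests to be ignored. The plan should be changed, but this does not undermine its time-to-diabetes analysis.

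**What to change.** Replace the sentence on repeated measures with a linear mixed model for each continuous outcome, with arm, visit, arm-by-visit and baseline value, and with skewed markers transformed. Include every randomised participant with at least one follow-up value. Report the arm difference at a named visit with its 95% confidence interval. State the missing-at-random assumption and add a sensitivity analysis, because participants with no follow-up value at all still fall outside this model.

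For repeated binary outcomes use a mixed logistic model or GEE, noting that standard GEE needs a stronger missing-data assumption. Restrict Friedman's test to describing change within an arm.

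The cost is a change of wording and slightly more analysis work. "Data will be analyzed using the Statistical Package for Social Studies (SPSS 22; IBM Corp., New York, NY, USA"), and that package can fit these models. No extra data or visits are needed. The main downside is reliance on missing-at-random, which the data cannot verify.

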### Behavioral change

As per the TTM [24], participants will be classified into five stages of changes (precontemplation (PC), contemplation (C), preparation, action, and maintenance) (Table 1) at the baseline visit and then every month during the first 6-month follow-up visit, through the WhatsApp application in the participants’ smartphones. This will test whether the sent messages were appropriate for the stage of behavioral change. This evaluation will be updated based on self-reported questions, which will be given to the participants separately and sent back to the research team through the WhatsApp application.

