### Time of messaging

The messages will be sent to the intervention group only in the first 6 months from the baseline. The following time points measure the intervention’s long-term effect on biological markers, and the stages of change for healthy eating and physical activity.

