### Measuring the TTM stage of change, the effect of intervention in the long term

The TTM stage of change for physical activity and a healthy diet is determined at the baseline using a question adjunct to the WHO STEPS questionnaire. At the baseline visit and every month, the adjunct questions will be delivered to the participants’ smartphone through the WhatsApp application. This will detect progress in the stage of change and help us move on to the next set of messages accordingly. The WHO STEPS questionnaire will be administered at every 6-month follow-up visit to measure the interventions’ long-term effects on biological markers and changes towards a healthy diet and physical activity.

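### The log-rank comparison of stage-of-change transitions and relapses does not suit a reversible outcome, compares relapse in a largely post-randomisation subset, and loses its 5% level if only the intervention arm's monthly staging is used

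*Protocol article*

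**What the plan says.** Under *Data analysis plan*, Kaplan-Meier curves and log-rank tests compare the arms and risk groups for progression to diabetes and also for "transition and/or relapses from different stages of TTM". The same section says that the principal analyses of primary and secondary outcomes are by intention to treat.

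Stage is measured on two schedules.

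- **Monthly.** Under *Behavioral change*, participants are classified "at the baseline visit and then every month during the first 6-month follow-up visit, through the WhatsApp application", and the stated reason is: "This will test whether the sent messages were appropriate for the stage of behavioral change". The section on measuring the stage of change says: "At the baseline visit and every month, the adjunct questions will be delivered to the participants’ smartphone through the WhatsApp application". It adds: "This will detect progress in the stage of change and help us move on to the next set of messages accordingly". Neither section names an arm.
- **Six-monthly.** Under *Assessment of interventions*, all participants are staged at baseline and at each follow-up visit. The TTM outcome is the first one listed under the heading for secondary outcomes at the 6-month visits.

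*Time of messaging* says who gets messages: "The messages will be sent to the intervention group only in the first 6 months from the baseline".

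**The concern.** There are three separate problems.

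1. **One-time event, reversible state.** Kaplan-Meier and log-rank follow each person to one event. Table 1 and the analysis sentence itself both foresee relapse. On a first-event curve, someone who reaches action and falls back counts the same as someone who stays there.
2. **Relapse risk set.** Only a person in action or maintenance can relapse from it. If the messages work, more people in the intervention arm enter that risk set, and different people. A log-rank test among them is not a comparison of the randomised groups.
3. **Detection frequency.** Both stated uses of monthly staging concern people who receive messages. If controls are staged only at 6-monthly visits and both kinds of data enter the test, a control's change in month 2 is dated month 6, or is missed if it has reversed by then. The same change in the intervention arm is dated month 2.

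At stake is the first listed secondary outcome, which is also the mechanism by which the intervention is meant to act.

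**Working it through.** The article gives no figure for the stage analysis (its sample size concerns diabetes incidence), so there is nothing to reproduce. Problems 1 and 2 follow from reading the sections together. Problem 3 can be sized by simulating trials with no arm effect.

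**Inputs from the article:** 150 per arm; 5% level, taken as two-sided; five stages; visits every 6 months to month 36, as in the Abstract; monthly staging in months 1 to 6.

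**Assumptions, not in the article:** baseline mix of 25/35/25/10/5% from precontemplation to maintenance; monthly probability of moving one stage forward/backward of 0.05/0.02, 0.10/0.05, 0.15/0.10 or 0.20/0.20, identical in both arms; no dropout; 1000 trials per cell.

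**Test:** Z = Σ(O₁ − E₁)/√ΣV, with E₁ = d·n₁/n and V = d·(n₁/n)(1 − n₁/n)(n − d)/(n − 1) at each event time. Reject if |Z| > 1.96.

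**Events:** (a) first recorded action or maintenance, among those below action at baseline; (b) first recorded stage different from baseline; (c) first recorded backward move, counted in everyone. Because (c) includes everyone, its figures do not contain the subset problem, which comes on top.

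**Proportion of null trials rejected**

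| Forward/backward | Event | Both arms monthly, then 6-monthly | Both arms 6-monthly | Intervention monthly, control 6-monthly |
|---|---|---|---|---|
| 0.05/0.02 | a | 0.050 | 0.047 | 0.052 |
| | b | 0.044 | 0.034 | 0.151 |
| | c | 0.057 | 0.052 | 0.077 |
| 0.10/0.05 | a | 0.051 | 0.045 | 0.064 |
| | b | 0.051 | 0.052 | 0.925 |
| | c | 0.054 | 0.042 | 0.248 |
| 0.15/0.10 | a | 0.049 | 0.058 | 0.087 |
| | b | 0.051 | 0.054 | 1.000 |
| | c | 0.052 | 0.050 | 0.856 |
| 0.20/0.20 | a | 0.052 | 0.053 | 0.205 |
| | b | 0.051 | 0.047 | 1.000 |
| | c | 0.049 | 0.033 | 1.000 |

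The simulation error at a true 5% is √(0.05 × 0.95/1000) = 0.007, so values from about 0.036 to 0.064 are compatible with 5%. No common-schedule cell exceeds that range. With unequal schedules, event (a) departs clearly from 5% only in the two fastest settings, while (b) and (c) are inflated in every setting.

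Much of the inflation comes from timing. At 0.10/0.05, 97% of both arms have a recorded change by month 36, yet the test rejects in 0.925 of trials because the intervention arm's changes are dated earlier. For backward moves the counts also differ slightly: 68% recorded against 64%.

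**The case against.** A reader might infer that reversible stages plus monthly staging are enough to produce a false arm difference. They are not: on a common schedule, monthly or 6-monthly, the test keeps its level. Time to first transition is a legitimate quantity for a reversible state; it is incomplete rather than invalid.

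A reader might also infer that controls are not staged monthly. The article never says so. It speaks of participants without naming an arm, although elsewhere it usually says when something is limited to the intervention group. The message-steering purpose makes staging in one arm only a strong inference, but still an inference. The heading of the secondary outcomes points to the 6-month visits, and nothing says that WhatsApp data enter the log-rank test.

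The largest rates belong to any change or any backward move. The listed outcome is change towards action and maintenance, for which inflation runs from none to about 0.21. All of these rates depend on assumed transition probabilities. Finally, the exact event and data source may be set out in a fuller document, and the plan also lists chi-square and repeated-measures methods.

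All of this stands, and it makes the false-positive risk conditional. It does not answer the first two problems. The article positively commits to a survival comparison of transitions and relapses, and no choice of schedule turns relapse among progressors into a randomised comparison. The exclusion of people who already exercise more than 50 minutes a week or follow a diet regimen suggests that few will start in action or maintenance, so the relapse risk set would form mostly after randomisation.

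**Conclusion.** The point holds in a limited form. Without any assumption, the planned method discards later moves in a reversible outcome, and its relapse comparison rests largely on a post-randomisation subset, at odds with the stated intention-to-treat principle.

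Conditionally, if monthly data are collected or used in the intervention arm alone, the test can exceed 5% with no true effect: from 0.05 to 0.21 for first action or maintenance, 0.15 to 1.00 for any change, and 0.08 to 1.00 for any backward move. These ranges rest on the assumed transition rates and baseline mix. The documents do not support saying that the test as planned is inflated, because they leave open both who is staged monthly and which data are used. The matter affects a secondary outcome and does not touch the diabetes incidence analysis. It should be corrected.

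**What to change.** - Base the between-arm stage comparison on the stage held at the scheduled 6-monthly visits, in all randomised participants. Use a mixed logistic model for being in action or maintenance, or an ordinal mixed model for stage, with arm, visit and baseline stage.
- Remove TTM stages from the log-rank sentence.
- Use the monthly WhatsApp data only to steer messages, and state whether controls receive the monthly questions.
- Define relapse as a drop from action or maintenance at one visit to a lower stage at a later visit, and report it descriptively. If an arm comparison is wanted, use a composite state defined for everyone randomised, such as having reached and sustained action or maintenance. Counting everyone below action as relapsed would not do: it includes people who never progressed and is only the complement of the action/maintenance proportion.

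The cost is a change of wording. The visit data are already planned in both arms. What is given up is the monthly timing of transitions.

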### Sample size calculation

A sample size of 300 is required so that there are 150 participants each in the intervention and control groups. The sample size was calculated by using Stata® software version 15 (StataCorp, College Station, Texas, USA) with the assumptions that α = level of significance (0.05), β = Type II error (power of the study = 1- β = 80%). The hazard rate of diabetes development among the control group is 10% over the 2 years, the hazard rate of diabetes development among the intervention group is 7% over the 2 years (reduction of about 30%) and the minimum sample size required to reject the null hypothesis is 256 (128 in each group). With an expected loss of follow-up around 20%, the sample size was increased to 300 participants in total.

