## Background

Impaired glucose tolerance (IGT) and impaired fasting glucose (IFG) are intermediate conditions sometimes called prediabetes, where blood glucose levels are above normal but below diabetic thresholds [1]. Seventy percent of individuals with prediabetes eventually develop type 2 diabetes mellitus (T2DM) [2]. While people with IFG have a 20–30% chance of developing diabetes over the course of 5–10 years [3–5], this chance escalates to 90% if the individual is diagnosed with IGT [6]. In Saudi Arabia, the prevalence of both prediabetes and T2DM is high (18.3 and 11.9%, respectively) and increases with age [7]. Even though T2DM is treatable, it is usually associated with other comorbidities such as hypertension, hypercholesterolemia and obesity. These conditions in patients with T2DM contribute to the development of cardiovascular diseases (CVD). Thus, T2DM is one of the modifiable risk factors that can decrease the risk of several chronic diseases such as CVD, and reduce its associated mortalities. A population-based study from England showed that prediabetes may convert back to normal glycemia [8]. Furthermore, landmark clinical trials have proven the effectiveness of lifestyle interventions towards a healthy diet and sufficient physical activity to reduce or delay the occurrence of T2DM by 50% in prediabetic individuals [9–11]. The Center For Disease Control and Prevention (CDC), and the American College of Sports Medicine have demonstrated that accumulation of 10,000 steps per day on most days of the week is an important component of improving glycemic control, insulin sensitivity, and/or cardiovascular (CV) risk in patients with T2DM [1, 12].

Targeting this at risk population of prediabetics and increasing their awareness about the importance of a healthy lifestyle will help in the long run, to significantly decrease the prevalence of T2DM in Saudi Arabia. While many educational programs have been used to promote health in the Saudi community, the use of a digital approach is still in its early stages [7]. Nowadays, the daily use of smartphones is vital due to their efficiency, connectivity and functionality. This makes the delivery of educational messages easier and more convenient.

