## Methods/design

### Study design (setting, eligibility and recruitment)

This is a three-year randomized controlled trial that includes Saudis ≥18 years of age. Participants for the present study will be recruited from the Heart Health Promotion study (HHP), which was conducted at King Saud University from 8 July, 2013 to 30 April, 2014 [20]. In the HHP study, participants were recruited from the three primary health care clinics serving the employees and their families at King Khalid University Hospital [20]. The HHP study was conducted on a large group of Saudi adults, who were at a higher risk of developing T2DM within 2–3 years. Recent data record updates of the original study on May 2017, revealed that out of the total sample (1234 prediabetic subjects) enrolled in the HHP study, 218 individuals had developed overt diabetes during the last 4 years (May 2013–May 2017). Therefore, 1016 are eligible for the present study.

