### Baseline visit

#### Lifestyle education

Eligible prediabetic subjects from the previous HHP study [20] will be invited to the HHP office. If they give consent for this trial, then participants will be assigned to either the intervention or the control group by the computer-generated list. At this baseline visit, all participants will receive group education and motivation about lifestyle modifications along with written information about diet and physical activity recommendations offered by a diabetic educator and a physician. This will advise participants on balancing food intake and physical activity to achieve and maintain appropriate body weight. All participants will take Metformin 500 mg twice daily. In addition, only participants in the intervention group will receive SMS messages at frequent intervals. These messages will be about a healthy lifestyle, the benefits of physical activity and a healthy diet. Neither group will receive any additional lifestyle information or advice by personal contact after the baseline visit, except in response to specific queries from the participants.

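### The 10% control rate in the sample size section makes no visible allowance for the metformin and education that controls receive, which further weakens a power claim that already fails at 10% versus 7%

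*Protocol article*

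**What the plan says.** The Sample size calculation sets the control arm as follows: "The hazard rate of diabetes development among the control group is 10% over the 2 years". The intervention arm is set at 7%, a relative reduction of about 30%. With alpha 0.05 and 80% power, the section arrives at 256 participants and raises this to 300 for loss to follow-up. It does not mention treatment given to both arms.

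Under Lifestyle education, the baseline visit gives both arms the same background care: "all participants will receive group education and motivation about lifestyle modifications along with written information about diet and physical activity recommendations", and "All participants will take Metformin 500 mg twice daily". Only the text messages differ between arms.

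The one progression figure reported for this population is in the Study design section, where, of 1234 prediabetic members of the Heart Health Promotion (HHP) cohort, "218 individuals had developed overt diabetes during the last 4 years (May 2013–May 2017"). The 1016 who had not progressed form the recruitment pool. The same section dates the HHP study from 8 July 2013 to 30 April 2014.

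**The concern.** A control rate for sizing should describe the control arm that will be run. Here the assumed rate is about the cohort's rate before the trial, while the trial's controls receive a drug, group education and written advice. The article's Background credits lifestyle interventions in landmark trials with the ability "to reduce or delay the occurrence of T2DM by 50% in prediabetic individuals", so by its own reasoning care of this kind can lower progression. The sizing does not say whether 10% already reflects it, nor that the effect under test is what the messages add to it.

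The power of the planned log-rank and Cox comparisons depends on the number of events. If the background care works, there are fewer events than the stated rates imply, and a null diabetes result says less than the stated 80% power would suggest.

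**Working it through.** **1. The plan's own figure.** 256 can be reproduced. Take the two-sided test of a difference between two exponential hazards, h1 = 0.10 and h2 = 0.07, mean 0.085, 1:1 allocation, with no censoring:

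N = [1.960·√(4·0.085²) + 0.842·√(2·0.10² + 2·0.07²)]² / (0.10 − 0.07)² = (0.3332 + 0.1453)² / 0.0009 = 254.4, rounded up to 128 per arm, or 256.

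Without censoring, every participant has the event, so 256 is in effect a count of events. The Freedman formula at a hazard ratio of 0.70 gives 253 events and the Schoenfeld formula gives 247. At a fixed ratio the formula does not depend on the control rate: with 0.0926 or 0.05 as the control hazard and the ratio kept at 0.70, it still returns 256.

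If 10% and 7% are read as the proportions who develop diabetes, the two-proportion formula requires 2712 participants. Dividing 247 events by the mean event probability gives 2888.

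**2. The source cohort's rate.** 218/1234 = 17.67%.

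- Nominal four years, constant hazard: 1 − (1 − 0.1767)^(2/4) = 9.3% over two years. The 95% confidence interval is about 8.1% to 10.4%.
- Enrolment from July 2013 to April 2014 gives about 3.83 to 3.05 years of follow-up to May 2017: 1 − (1 − 0.1767)^(2/3.83) = 9.7%, and 1 − (1 − 0.1767)^(2/3.05) = 12.0%.

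So 10% is about the cohort's pre-trial rate.

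**3. Expected events and power.** Read 10% as the two-year risk in controls and keep the hazard ratio at 0.70, with two-sided alpha 0.05 and no loss to follow-up:

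- intervention risk = 1 − (1 − control risk)^0.70
- events = N/2 × (control risk + intervention risk)
- z = |ln 0.70| × √(events/4)
- power = Φ(z − 1.96) + Φ(−z − 1.96)

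Example at 10% with N = 300: the intervention risk is 7.1%; events = 150 × (0.100 + 0.0711) = 25.7; z = 0.3567 × √6.42 = 0.90; power = 15%.

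| Control risk, 2 years | Basis | N = 300, 2 years: events, power | N = 1016, 2 years: events, power | N = 1016, 3 years: power |
|---|---|---|---|---|
| 12% | cohort, shortest follow-up | 30.8, 17% | 104.4, 45% | 60% |
| 10% | the plan | 25.7, 15% | 86.9, 38% | 52% |
| 9.3% | cohort, nominal 4 years | 23.8, 14% | 80.5, 36% | 49% |
| 7% | assumed benefit of control care | 17.9, 12% | 60.7, 28% | 39% |
| 5% | assumed larger benefit | 12.8, 10% | 43.3, 22% | 30% |

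The 7% and 5% rows are assumptions, because the article gives no metformin effect and no estimate for one education session. The three-year column extends the same hazards to the planned trial length.

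**4. What the control rate changes once events and participants are told apart.** The two-proportion requirement at a 30% relative reduction is 2712 participants at a control rate of 10%, 3982 at 7% and 5676 at 5%. Correcting the formula while keeping 10% would leave this dependence unaddressed.

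**The case against.** **The cohort's care is not described.** Its members came from primary care clinics serving university employees and their families, and the Intervention section calls one level of the trial's intervention the standard care of the university's primary health care services. Education may not be new to them, and prior metformin use is not reported. This stands, and it means that the size of any fall in the rate is unknown.

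**Some features push the rate up.** The trial excludes people who exercise more than 50 minutes a week or follow a diet regimen. Participants are older than when they entered the cohort. Diabetes is sought by HbA1c every six months, whereas the cohort count came from a record update. This also stands: the net direction is not settled, and any range shown should extend above 10%.

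**The 50% figure does not transfer.** It refers to lifestyle interventions in landmark trials, whereas controls here get one baseline education session and no further personal advice except in reply to queries. It cannot serve as the estimated benefit of control care.

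**A condensed article may omit the source of an input.** Agreed; a missing citation is not the point. The point is that the article states the rate and describes the control care, and the one takes no visible account of the other.

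**A stronger reading is tempting:** that the plan sets treated controls above the rate seen in the untreated cohort, and so sizes against the wrong comparator. The documents do not support this. No two-year rate was observed. The 9.3% is derived, its interval includes 10%, and the enrolment dates move it to about 9.7% to 12%. The article also gives no planned event count that could be missed.

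**Conclusion.** The point holds in a limited form. The control rate of 10% is about the source cohort's pre-trial rate, and the sizing shows no allowance for the metformin, group education and written advice given to all controls. If that care lowers progression, power falls from 38% to 28% (control rate 7%) or 22% (5%) with 1016 participants over two years, and from 15% to 12% or 10% with 300. These figures assume a hazard ratio of 0.70, constant hazards, two-sided alpha 0.05 and no loss; the lower control rates are illustrations.

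A reader might infer that the control rate is what defeats the 80% claim. It is not. The claim already fails at the plan's own 10% versus 7%, because an event requirement was used as a participant count, and replacing 10% by 9.3% costs only about one to two points. The control-rate point is real, worth correcting and secondary to that error.

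**What to change.** In the Sample size calculation:

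- Give the basis of the control rate for the control arm as delivered. If it starts from the HHP figure, state the follow-up time used and the allowance made for care given to both arms.
- State that the effect under test is what the text messages add to that care.
- Replace the 80% claim with expected events and power at the actual enrolment over a range of control rates, for example 5% to 12%, with the lower end labelled as an assumption about the benefit of control care. A range that stops at 9.3% would be biased low.
- Make this change together with the correction of 256 from participants to events.

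In the Data analysis plan, say that a null diabetes result will be interpreted through the confidence interval of the hazard ratio and not as evidence of no effect.

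The cost is a reworded section and a short recalculation. No extra patients are needed and treatment does not change. The downside is a less favourable stated power.
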